**Methods/design:**

This study is a single-centre randomised controlled trial being performed in a tertiary hospital in The Netherlands. From among cases of a suboptimal or abnormal foetal heart rate pattern during the second stage of term labour, a total of 116 patients will be randomised to the control group, where normal care is provided, or to the intervention group, where before normal care 100% oxygen is supplied to the mother by a non-rebreathing mask until delivery. The primary outcome is change in foetal heart rate pattern. Secondary outcomes are Apgar score, mode of delivery, admission to the neonatal intensive care unit and maternal side effects. In addition, blood gas values and malondialdehyde are determined in umbilical cord blood.

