## Background

Labour contractions cause alterations in intrauterine pressure and can thereby affect uterine and umbilical blood flow [1–5]. These fluctuations in blood flow towards the foetus can negatively influence oxygen flow and blood pressure [1–5]. Through chemo- and baroreceptor responses, these changes in foetal oxygenation and blood pressure affect foetal heart rate (FHR) [1, 2, 6, 7]. Hence, non-reassuring FHR patterns such as FHR decelerations may be a sign of foetal hypoxia [8–10]. Prolonged foetal hypoxia may lead to an increased risk of foetal morbidity, including renal insufficiency, pulmonary hypertension, necrotising enterocolitis and hypoxic–ischemic encephalopathy and foetal death [11, 12]. A prospective cohort study of term neonates in 2010 showed that 48% of admissions of these neonates to neonatal intensive care units (NICUs) were related to perinatal asphyxia (defined by the authors as a 5-minute Apgar score < 7). The neonatal mortality rate was 8% in this study, the largest proportion of which (71%, *n* = 12 of 17) was related to asphyxia [13].

Methods to directly measure foetal oxygenation during labour are unavailable, whereas methods for the continuous intrapartum monitoring of pH, oxygen saturation (SpO_2_), partial carbon dioxide pressure (pCO_2_) and partial oxygen pressure (pO_2_) are not yet suitable for clinical practice [14–16]. Therefore, the cardiotocogram (CTG), with occasional foetal scalp blood sampling (FSBS), is still the method of first choice to estimate foetal well-being during labour. The CTG has very good specificity but poor sensitivity for foetal well-being [17]. In other words, if the FHR pattern is reassuring, the foetus is very likely to be well-oxygenated. However, when FHR patterns are non-reassuring, the foetal condition is unclear, and foetal distress cannot be ruled out.

Instead of aiming for immediate delivery in the presence of suspected foetal distress, one may try to improve foetal oxygenation to avoid an invasive intervention. Several intrauterine resuscitation techniques are used in clinical practice and have been described in the literature [18, 19]. However, robust evidence regarding their effect on neonatal outcome is limited [18]. One of the interventions that still raises discussion is the administration of additional oxygen to the mother to treat foetal distress during labour [18, 20–23].

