Another frequently stated argument to discourage maternal hyperoxygenation as standard care is the potential increase in free oxygen radicals in both mother and foetus [35, 36]. An increase in the markers for free oxygen radical production has been seen for the use of high fractions of inspired oxygen and in the presence of non-reassuring FHR patterns [35–38]. Also, lipid peroxide concentrations in arterial cord blood are higher after uncomplicated vaginal delivery than after elective caesarean section [39].

To a certain degree, free oxygen radicals are physiological and known to be higher in the presence of several maternal and foetal conditions, such as pre-eclampsia, diabetes, smoking, intrauterine growth restriction and foetal distress [37, 39–42]. The effect of maternal hyperoxygenation on free oxygen radical release, in response to non-reassuring foetal status, has not yet been investigated.

What we do know is that neonatal resuscitation with 100% oxygen may lead to an increase in neonatal mortality and morbidity, including bronchopulmonary disease and retinopathy, mainly in premature infants [43–46]. However, the increase in foetal pO_2_ due to maternal hyperoxygenation will never reach the levels obtained by the direct application of 100% oxygen directly to the foetus [23]. To our knowledge, the clinical implication of increased free radical production due to maternal hyperoxygenation has not been investigated. Researchers in studies using maternal hyperoxygenation as a treatment for the growth restricted foetus did not report any harmful effects [47, 48].

With regard to the mother, some potential side effects have to be taken into account. The use of high fractions of inspired oxygen in the absence of tissue hypoxia may cause toxic effects as a result of oxidative stress [49, 50]. This may lead to, for example, mucosal inflammation, hypoperfusion and pneumonitis [51]. A reversible vasoconstriction of approximately 10% in the maternal brain has been described [52]. However, this is not expected to cause any harm [53, 54]. Administration of 100% oxygen during labour is not investigated. However, it has been well investigated for the treatment of cluster headaches, and no severe side effects (e.g., hypoventilation and fainting) have been reported [54].

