### Patient recruitment and randomisation

All patients eligible to be included in this study will be asked antepartum to participate when they visit the outpatient clinic or when they are admitted to the delivery ward. All patients will receive oral and written information about the study from the attending midwife or doctor or from a co-investigator (Additional files 2 and 3). After informed consent is obtained, and only in case of suboptimal or abnormal FHR patterns during the second stage of labour, randomisation is performed using sealed opaque envelops. The allocation sequence is computer-generated using random blocks of four or six patients.

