#### Maternal outcome

Maternal outcome measures include the mode of delivery, side effects and reasons for discontinuation of oxygen administration. Side effects include headache, dizziness, discomfort of the non-rebreathing mask and any other complaint mentioned by the participant. The delivery room staff will register on the case report form if the parturient experiences any side effects and/or if there are reasons for eventual discontinuation of oxygen administration. Also, to gain insight into how labouring women experience receiving additional oxygen via a non-rebreathing mask compared with receiving normal care, a short questionnaire will be used to investigate experiences of all the participants with this study.

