### Hypothesis

We hypothesise that maternal hyperoxygenation will improve FHR, without any severe maternal side effects. We do not expect a difference in rates of vacuum-assisted delivery or secondary caesarean sections or in Apgar scores or umbilical cord pH values, owing to the relatively small sample size. Furthermore, we expect larger concentrations of MDA in the intervention group than in the control group.

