In this study, we focus on the foetal condition during the second stage of labour and short-term neonatal outcome. This implies that abnormalities in FHR patterns during the first stage of labour are not taken into account. We believe that the randomisation process will limit its influence. With regard to the neonatal period, we did not arrange long-term follow-up, because we do not expect any clinically relevant side effects that can be attributed to maternal hyperoxygenation. Besides, the sample size is too small to draw firm conclusions on long-term neonatal effects in this study.

Power analysis of the present study is based on the expected effect on the primary outcome measure, and the study is not powered to find any significant differences in Apgar score and umbilical cord blood gas values. In the power analysis, we used an expected improvement in deceleration depth and duration of 50%. On one hand, this value is based on small non-randomised studies and may be overestimated. On the other hand, those studies provide the only available data. Also, we believe it is unlikely that a limited improvement in deceleration depth and duration has clinical relevance. The sample size is calculated for each of the subgroups of suboptimal and abnormal FHR tracings. We believe it is important to assess the effect of the intervention in these subgroups because foetuses with lower initial pO_2_ levels may profit more from maternal hyperoxygenation [29].

Regarding the subgroups of AGA and SGA infants, we did not increase our sample size to reach an adequate number of participants in the SGA group. Nevertheless, we find it interesting to investigate whether there is a different effect of maternal hyperoxygenation in SGA infants compared with AGA infants.

Because of organisational challenges, it is not possible to conduct a double-blind trial. Hence patients and delivery room staff are not blinded to the patient’s allocation to a study group, which may lead to observer bias. However, analysis of FHR tracings will be done using a computerised algorithm, to minimise bias, and the investigators judging the CTGs and secondary outcome measures are blinded to the study arm.

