To investigate the effect of maternal hyperoxygenation in the presence of foetal distress on the release of free oxygen radicals, MDA is estimated in umbilical cord blood. MDA is the peroxidation product of membrane polyunsaturated fatty acids. We chose to measure this marker for oxidative stress because it was used in prior studies performed during labour and it is related to vaginal birth, non-reassuring FHR tracings, maternal hyperoxygenation and acidaemia in arterial cord blood [36, 37, 39, 41]. We realise that differences in values in umbilical cord blood may be confounded by mode and duration of delivery; therefore, we will correct the results for the mode of delivery. A practical ground on which to choose this marker is that it is the only marker for oxidative stress that can be estimated accurately in Dutch laboratories. In the intervention group, oxygen administration will be continued until delivery to enable analysis of its effect on cord blood gas values and MDA.

Despite some important limitations of this study, we believe this is the best possible way to perform a study while restricting safety issues. If the results do not show any improvement in FHR, we believe that maternal hyperoxygenation should not be used as a treatment for foetal distress. However, if a beneficial effect is demonstrated, we will design a multicentre RCT to investigate the effect on neonatal outcome.

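### The MDA comparison is to be corrected for mode of delivery, a post-randomisation outcome that cannot confound it and whose adjustment can introduce bias

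*Protocol article*

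**What the plan says.** The only analysis rule specific to MDA is in the protocol article, Discussion: cord-blood differences "may be confounded by mode and duration of delivery; therefore, we will correct the results for the mode of delivery". Duration is named beside mode, but only mode is to be corrected for.

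Other sections fix the order of events and the role of the variable:

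- Patient recruitment and randomisation: "only in case of suboptimal or abnormal FHR patterns during the second stage of labour, randomisation is performed using sealed opaque envelops". Mode of delivery is not yet settled at that point.
- Abstract, Methods/design: "Secondary outcomes are Apgar score, mode of delivery, admission to the neonatal intensive care unit and maternal side effects".
- Maternal outcome: "Maternal outcome measures include the mode of delivery, side effects and reasons for discontinuation of oxygen administration".
- Hypothesis, on the direction for MDA: "we expect larger concentrations of MDA in the intervention group than in the control group". The same section expects no difference in vacuum or secondary caesarean rates and gives the small sample size as the reason.

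**The concern.** A confounder of a treatment comparison is a common cause of treatment and outcome. Allocation here is by sealed envelope during the second stage, so nothing that happens later can have influenced it. Mode of delivery therefore cannot confound the comparison by allocated arm. It can play two other roles:

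- **Mediator.** Oxygen may change how the baby is delivered, and mode may change MDA. Holding mode fixed removes that part of the effect.
- **Collider.** Allocation and foetal compromise may both influence mode. Conditioning on mode then makes allocation and compromise appear associated, and if compromise also influences MDA, a non-causal path opens.

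If either applies, the corrected coefficient is not the total effect of allocation. If unmeasured compromise matters, it is not the direct effect either. MDA is the only oxidative-stress marker in the trial, and the Discussion calls free oxygen radicals a major concern, so the estimate will feed the judgement of benefit against harm. Calling it a safety comparison would be a fair description, though the document lists MDA as a neonatal outcome.

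**Working it through.** **1. Does the document support the links?** It states no figure for the MDA comparison, so there is nothing to reproduce. The links have to be read from the text.

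- *Oxygen to mode.* The Background gives the rationale for resuscitation: "one may try to improve foetal oxygenation to avoid an invasive intervention".
- *Knowledge of allocation to mode.* The Discussion says "patients and delivery room staff are not blinded" to allocation.
- *Mode to marker.* The summary of clinical findings reports that "lipid peroxide concentrations in arterial cord blood are higher after uncomplicated vaginal delivery than after elective caesarean section". The Discussion also relates MDA to vaginal birth. Nothing is said about vacuum delivery.
- *Compromise to marker.* The Discussion relates MDA to non-reassuring tracings and to acidaemia.
- *Compromise to mode.* This is my inference; the document does not state it.

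**2. How large could the shift be?** Every input here is an assumption. A is allocation to oxygen, U is unmeasured compromise (standard normal), M is operative delivery, and e is standard normal noise, so the residual SD is 1:

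logit P(M = 1) = −0.4 + bU·U + bA·A

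MDA = gU·U + gM·M + e

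Oxygen has no direct effect on MDA in this model. Ranges: bU 0.7 to 1.5, bA −0.4 to −1.2 (and 0 as a check), gU 0.4 to 0.7, gM 0, +0.3 or −0.3. Each scenario has 2,000,000 records. MDA is regressed on A alone (total effect) and on A plus M (corrected). Results are in residual SD:

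| bU, bA, gU | gM | Operative, control / oxygen | By arm only | Corrected for mode |
|---|---|---|---|---|
| any, bA = 0 | any | equal, 41–43% | 0.00 | 0.00 |
| 0.7, −0.4, 0.4 | 0 | 41% / 33% | 0.00 | 0.02 |
| 1.5, −1.2, 0.7 | 0 | 43% / 24% | 0.00 | 0.145 |
| 0.7, −0.4, 0.4 | +0.3 | 41% / 33% | −0.03 | 0.02 |
| 1.5, −1.2, 0.7 | +0.3 | 43% / 24% | −0.06 | 0.145 |
| 0.7, −0.4, 0.4 | −0.3 | 41% / 33% | 0.025 | 0.02 |
| 1.5, −1.2, 0.7 | −0.3 | 43% / 24% | 0.055 | 0.14 |

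The by-arm estimate gives the total effect throughout. The corrected estimate should be 0 if it recovered the direct effect. Instead it runs from about 0.02 to 0.145 whenever oxygen changes mode. When oxygen does not change mode, the two estimates agree.

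**3. In units of the total SD.** With gM = 0 and gU = 0.7 the total SD is √(1 + 0.7²) = 1.22, so 0.145 / 1.22 = 0.12.

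**4. Against the trial's precision.** The standard error of a difference in means, in total SD, is √(2/n) with n per arm. The article gives two totals:

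- 116 (Abstract), so n = 58: √(2/58) = 0.19.
- 162 (Sample size calculation), so n = 81: √(2/81) = 0.16.

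The largest spurious shift, 0.12, is below both. Missing samples would make the standard errors larger. The gap from the *total* effect can be wider: in the fifth row it is 0.145 + 0.056 = 0.20 residual SD, or 0.20 / 1.27 = 0.16 total SD, about one standard error with 81 per arm. That corner needs operative delivery to raise MDA, which the document does not support.

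**The case against.** **No effect on mode is expected.** The Hypothesis section foresees no difference in vacuum or caesarean rates, and without one the correction is harmless. The second part stands: the problem is conditional on allocation changing mode. The first part carries less weight, because the reason given is the small sample size. That bears on what can be detected, not on whether an effect exists.

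**The correction may not replace the plain comparison.** This is one Discussion sentence in a condensed article. The Data analysis section prescribes intention-to-treat and per-protocol analyses and does not limit them to the primary outcome. This softens the point without removing it: the sentence is a firm commitment with a stated reason, and no unadjusted MDA comparison is named as the main one. Confounding is a more natural worry in the per-protocol comparison of women who did and did not receive oxygen. The sentence is not restricted to that comparison, however, and mode still follows the oxygen.

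**Precision.** Mode may explain variation in MDA. Precision is not the reason given, and pre-randomisation variables can serve that purpose without this risk.

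**The consequence is small.** This stands. MDA is a secondary outcome, the interim safety comparison does not use it, and the primary outcome and sample size are untouched.

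**A stronger reading to avoid.** A reader might infer from rows four and five of the table that the correction would turn a fall in MDA into an apparent rise. That needs operative delivery to raise MDA and oxygen to have no direct effect on it. The document links higher values to vaginal birth and expects a rise with oxygen. With gM = −0.3 both estimates are positive.

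**Conclusion.** The rule is wrong as written, and minor. That mode of delivery cannot confound the randomised comparison follows from the order of events alone and needs no assumption. That correcting for it *can* bias the MDA estimate depends on oxygen, or open-label knowledge of it, changing mode of delivery. The document makes this plausible but does not establish it.

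Size and direction cannot be derived from the document, which gives no operative delivery rate, no MDA variance and no effect of mode on MDA. Under the assumed inputs the spurious shift is about 0.02 to 0.145 residual SD, at most about 0.12 total SD and below one standard error. The upper end needs operative delivery to fall from about 43% to 24% together with strong unmeasured compromise. At the weaker effect on mode (bA = −0.4) the shift is about 0.02 to 0.05 residual SD. The documents do not support saying that the correction will bias the result or reverse its sign.

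**What to change.** Replace the Discussion sentence with a rule along these lines: the main MDA analysis compares the arms as allocated, unadjusted or adjusted only for variables fixed before randomisation (for example FHR category, parity and gestational age). Any analysis corrected for mode of delivery is labelled sensitivity or exploratory, with its assumptions stated, and MDA may be tabulated by mode and arm descriptively. Duration of delivery should not be added to the main model as a remedy, since the part after randomisation raises the same problem.

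The cost is a sentence or two of analysis wording. No new data are needed, and sample size, conduct and the primary analysis do not change.

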## Trial status

Patient recruitment started on 1 March 2016 and was estimated to be fulfilled on 31 March 2018.

## Abbreviations

AGA: Appropriate for gestational age
bpm: Beats per minute
CTG: Cardiotocogram
DC_PRSA_: Phase-rectified signal-averaging decelerative capacity
DNPH: 2,4-Dinitrophenylhydrazine
FHR: Foetal heart rate
FIGO: International Federation of Gynecology and Obstetrics
FSBS: Foetal scalp blood sampling
MDA: Malondialdehyde
*m/z*: Mass-to-charge ratio
NICU: Neonatal intensive care unit
pCO_2_: Partial carbon dioxide pressure
pHa: pH in arterial blood gas
pO_2_: Partial oxygen pressure
PRSA: Phase-rectified signal averaging
RCT: Randomised controlled trial
SAE: Serious adverse event
SGA: Small for gestational age
SPIRIT: Standard Protocol Items: Recommendations for Interventional Trials
SpO_2_: Oxygen saturation
SUSAR: Suspected unexpected serious adverse reaction
